## Abstract

**Background:**

Evidence based practice (EBP) requires that health professionals are competent in integrating the best evidence in their decision making. Being 'evidence-based’ requires skills and knowledge in epidemiology, biostatistics and information literacy. EBP is commonly taught in medical and health sciences degrees, yet there is little evidence to guide educators as to the best teaching modality to increase learner competency in EBP.

**Methods/design:**

This study is mixed methods in design. A randomised controlled trial will examine the effectiveness of blended learning versus didactic approach of teaching EBP to medical students. The primary outcome of the RCT is EBP competency as assessed by the Berlin tool. Focus groups will be conducted to explore student perceptions and attitudes towards implementing a blended learning approach in teaching EBP. A concurrent triangulation design will be implemented, permitting quantitative data to inform the effectiveness of the intervention and qualitative data to contextualise the results.

**Discussion:**

This study will provide novel evidence on the effectiveness of blended learning in teaching EBP to a cohort of undergraduate and graduate-entry medical students.

## Background

Evidence Based Practice (EBP), or evidence based medicine (EBM), has been adopted as a core unit across many medical schools worldwide, with a particular focus in Australian Universities [1]. The principles of EBP inform medical decision making by integrating the best available evidence with clinical expertise and patient values [2]. Adopting an evidence based approach to medicine requires that practitioners are competent in understanding and applying the following steps in clinical practice:

1. Asking a clinical question that is constructed using the PICO (patient, intervention, comparison, outcome) framework (ask);

2. Acquiring the evidence via a systematic and efficient search of the literature (acquire);

3. Appraising the evidence through application of critical appraisal techniques (appraise);

4. Applying the evidence to the clinical scenario (apply); and,

5. Assessing the EBP process as it relates to the clinical context (assess) [2].

Each step within the EBP process requires a different level of competency (i.e. integration of knowledge, skill, attitude and behaviour) from the practitioner [3]. Achieving a high level of competency in EBP can only be achieved when the practitioner is able to effectively undertake all five steps, which incorporate adequate levels of knowledge, skills, attitude and behavioural elements [3]. Achieving competency in the principles and practices of EBP provides the practitioner with the ability to know when and how to make evidence-based medical decisions, and also achieve lifelong learning within their medical discipline.

Each step of the EBP process requires a different competency to be learnt. This has led to the suggestion that different teaching modalities could be used in its implementation – be it lecture, tutorial, mini-course, problem based or online [4]. Limited evidence currently exists in order to inform educators as to the most effective method of teaching and increasing practitioner competency in EBP. A 2004 systematic review identified two randomised controlled trials (RCTs) and seven non-RCTs that examined the effectiveness of different teaching modalities in EBP [5]. The authors of that review concluded that standalone teaching improved student knowledge, but not skills, attitudes or behaviour in EBP. Conversely, evidence from the non-RCTs indicated that integrating teaching of EBP with clinical activities (i.e. blended learning) was associated with improvements across all four domains (i.e. knowledge, skills, attitudes and behaviour) [5].

A 2013 systematic review of the literature identified 9 RCTs that compared the effectiveness of various teaching modalities (lecture, tutorial, self-directed, online, problem-based, uni and multidisciplinary) in training medical students in EBM [6]. The review concluded that training in EBP increased student competency, but identified a lack of evidence to guide educators on which teaching modality is best at increasing EBM competency.

A variety of factors may dictate how an EBP course is implemented in medical education – be it student learning styles, infrastructure or other organisational issues. The ability to achieve competency in EBP also requires that students have a certain level of mastery in epidemiology, biostatistics, informatics and information literacy. Given the impact of these factors, and the challenge in achieving competency in a variety of areas, teaching EBP requires a multidimensional approach. Blended learning attempts to create an optimal learning environment by blended a variety of learning approaches (lecture, tutorial, online, problem-based etc.) [7].

## Methods/Design

### Aims

The aim of this study is to determine the effectiveness of blended versus didactic learning of EBP in medical students. The specific study objectives are to;

1. Determine the competency of students in EBP receiving EBP training via a blended learning approach compared to students receiving EBP training via a didactic approach, and;

2. Determine student self-efficacy, perceptions and attitudes on EBP teaching delivered through a blended learning approach.

### Design

This study is a mixed methods study, incorporating a randomised controlled trial and a qualitative case study at Monash University. A mixed methods approach will permit quantitative data to inform the effectiveness of the intervention, whilst qualitative data will contextualise those results addressing issues of 'how’ and 'why’ [8]. The protocol for this current study was informed by a pilot study on graduate-entry medical students, which has since been accepted for publication by BMC Medical Education.

### Settings and participants

A multi-campus study will be conducted with medical students currently enrolled in the MBBS course at Monash University. Monash University runs undergraduate and graduate-entry MBBS programs, in both Australia and Malaysia. Students are assigned to one of seven metropolitan hospitals, or six rural, hospitals in Australia (with one site in Malaysia). Participants for this study will be third year medical students, who are entering their first year of clinically-based training and first year of formal EBP training.

### Quantitative research methodology

The following outlines the protocol for the randomised controlled trial aspect of the study.

### Recruitment

Third year medical students are randomly placed in small tutorial groups for their EBP teaching (approximately 20–25 in a group). Tutorial groups will be randomised to receive EBP teaching adopting a blended learning approach, or the traditional didactic small group learning approach. Students not wishing to participate in the study will be taught via the traditional didactic approach and not be asked to complete an outcome assessment.

### Randomisation

Participants will be randomised according to their tutorial group (i.e. cluster) by a researcher independent to the study utilising a simple cluster randomisation procedure (computerised random numbers). All students will have access to the blended learning materials at the end of the study period to ensure parity between groups.

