### Analyses

#### Sample size calculation

A minimum of 120 students per arm (40 from each of metropolitan Melbourne (undergraduate), rural Victoria (graduate) and Monash Malaysia (international)), will be recruited to detect a 50% difference in EBP competency (α = 0.05, β = 0.80, σ = 2.8) between groups.

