#### Analyses

Quantitative data will be analysed using the principle of intention-to-treat. Mean differences in EBP competency, as determined by the Berlin tool, between intervention and control groups will be explored using a Student’s t-test. Differences between intervention/control groups and student type (undergraduate/graduate/international) will be explored using one and two-way ANOVA’s, where appropriate.

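### Simple, unstratified randomisation of tutorial groups does not guarantee the required 40 students per arm in each cohort, and at the stated minimum size is unlikely to deliver it

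*Protocol article*

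**What the plan says.** All of the following is in the protocol article.

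- **Randomisation.** The unit is the tutorial group: "Participants will be randomised according to their tutorial group (i.e. cluster"). The method is stated outright: "utilising a simple cluster randomisation procedure (computerised random numbers"). No stratification, blocking or matching by campus or student type is mentioned.
- **Recruitment.** Tutorial groups are small: "approximately 20–25 in a group". Their number is not given, either overall or by cohort.
- **Sample size calculation.** The target is set by arm and by cohort: "A minimum of 120 students per arm (40 from each of metropolitan Melbourne (undergraduate), rural Victoria (graduate) and Monash Malaysia (international").
- **Analyses.** Mean Berlin scores "between intervention and control groups will be explored using a" Student's t-test, with no cohort term. Cohort enters separately: "Differences between intervention/control groups and student type (undergraduate/graduate/international") are examined by one- and two-way ANOVA where suitable.
- **Discussion.** The study is expected to show how blended learning performs across the three kinds of student.

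**The concern.** The sample size section fixes how each arm is to be made up by cohort, while the randomisation section chooses a method that takes no account of cohort. Recruitment decides which students enter; only the allocation decides which arm a tutorial group joins. With groups of 20 to 25, a target of 40 per arm per cohort means about two groups per arm, and unrestricted randomisation balances poorly with so few units.

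Two things are at stake. If all of a cohort's groups land in one arm, that cohort offers no comparison of teaching methods, and no later adjustment can create one. If the split is merely uneven, the unadjusted t-test partly compares undergraduate, graduate-entry and international students, who also learn in different places.

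**Working it through.** **The plan's own figure.** 3 cohorts × 40 = 120 per arm, so the quota adds up. The power basis behind it cannot be rebuilt, because a percentage difference is given without a control mean. The check below does not depend on it.

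**Inputs.** Group size 20 to 25 (Recruitment); 40 per arm per cohort and three cohorts (Sample size calculation); simple allocation of groups (Randomisation).

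**Assumptions.** Each group lies within one cohort, which the settings suggest but do not state. Each cohort has the same number of groups, *k*. Every student takes part.

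**Groups needed.** 40/25 = 1.6 and 40/20 = 2, so two groups per arm per cohort. That gives *k* = 4 and 12 groups in all at the minimum. One group of 25 falls short of 40, so the quota is counted as met when every cohort has at least two groups in each arm.

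**Two readings of simple randomisation.**

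- *Equal arms forced:* a random list with half the groups in each arm. Each split (a, b, c) of the three cohorts has probability C(k,a)·C(k,b)·C(k,c) / C(3k,h), where a + b + c = h and h is half of 3k (rounded down).
- *Coin flips:* each group is allocated independently. The number in one arm within a cohort is binomial(k, ½), and the cohorts are independent.

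**At k = 4.**

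- Quota met (2:2 in all three cohorts). Forced: 6³/C(12,6) = 216/924 = 23.4%. Coin flips: (6/16)³ = 5.3%.
- Some cohort wholly in one arm. Forced: 132/924 = 14.3%, where 132 = 3 × (28 + 28) − 3 × 12. Coin flips: 1 − (14/16)³ = 33.0%.
- Under coin flips the overall split is not 6:6 with probability 1 − 924/4096 = 77.4%.

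**Range over the unstated group count (forced / coin flips).**

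| Groups per cohort | Quota met in all cohorts | Some cohort wholly in one arm |
|---|---|---|
| 4 | 23% / 5% | 14% / 33% |
| 5 | 47% / 24% | 6.8% / 17.6% |
| 6 | 72% / 48% | 2.5% / 9.1% |
| 8 | 93% / 80% | 0.4% / 2.3% |
| 10 | 99% / 94% | 0.1% / 0.6% |

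**Effect of a milder imbalance on the t-test.** Take k = 4, groups of equal size and 6:6 overall. If one cohort splits 3:1, it supplies 3/6 of one arm and 1/6 of the other. The raw arm difference then moves by 3/6 − 1/6 = 1/3 of that cohort's gap from the other two (taken as alike). A 4:0 split moves it by 4/6 = 2/3 of the gap. Under forced 6:6, a given cohort splits 3:1 or worse with probability 1 − C(4,2)·C(8,4)/C(12,6) = 1 − 420/924 = 54.5%. The article gives no figure for the gap between cohorts, so the shift in Berlin points cannot be stated.

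**After the change.** With allocation within cohort at k = 4, every cohort splits 2:2. That gives 40 to 50 students per arm per cohort and 120 to 150 per arm, before refusals.

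**The case against.** The strongest reply is that the number of groups is unknown and that 40 and 120 are minimums. The settings list seven metropolitan and six rural hospitals. If groups were formed by hospital, which is not stated, the two Australian cohorts would have at least seven and six groups; the Malaysian count would still be unknown. With 8 to 10 groups per cohort the quota is met in 80% to 99% of allocations, and a cohort wholly in one arm is rare. This stands, and it rules out saying that the method cannot deliver the quota or that gross imbalance is to be expected. At six groups, though, the quota is still missed in 28% to 52% of allocations.

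A reader might also infer that the two-way ANOVA fails if a cohort falls in one arm. That goes too far: a model with additive arm and cohort terms still estimates an arm effect from the other cohorts. What is lost is that cohort's own contrast and the full interaction.

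Nor is the imbalance a systematic bias. Randomisation makes it a matter of chance, and the ANOVAs do bring in student type. The main comparison is nevertheless the unadjusted t-test, so this answers the point only in part.

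Finally, the full protocol might stratify, and the quota might be only a recruitment target. The article, however, does not leave the method open. It names a simple procedure, and a recruitment target does not control allocation.

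**Conclusion.** The point holds as a mismatch between the stated allocation method and the stated composition of the arms. Simple randomisation does not guarantee 40 students per arm in each cohort. At the implied minimum of four groups per cohort it misses that composition in 77% (equal arms forced) to 95% (coin flips) of allocations, and some cohort lies wholly in one arm in 14% to 33%. Both risks shrink quickly as groups are added, and the second is small from about eight groups per cohort.

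These figures rest on groups lying within one cohort, equal group counts and full participation. Refusals would make the quota harder to meet: with groups of 20, a single refusal takes two groups below 40. The documents do not support the stronger claims that the quota is out of reach, that arm and cohort will usually be wholly confounded, or that no arm effect could be estimated. Since the article gives no group count that would make the risk small, and an empty arm within a cohort cannot be repaired afterwards, the change belongs before allocation.

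**What to change.** State the number of tutorial groups in each cohort. Randomise groups within cohort (metropolitan, rural, Malaysia), with equal numbers per arm or as near to equal as an odd count allows. The independent researcher should allocate the whole list at once, after the groups have been formed. Include cohort in the primary model, so that the analysis matches the allocation.

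The cost is small. The same computerised procedure is run by stratum, but the list of groups by cohort must be final before allocation. The article does not say when groups are formed relative to randomisation, so that order needs to be written down.

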### Control

Students randomised to the control group will receive the current didactic model of teaching EBP (lecture/tutorial) (Table 1). The didactic model consists of a 10 two-hour teaching sessions in which formal EBP concepts are delivered by a tutor/lecturer to students. The formal presentation is followed up by students performing a small group activity to consolidate their learning. This small group activity is commonly a critical appraisal of an article relating to the study design discussed by the lecturer/tutor i.e. therapy, harm, prognosis and diagnosis.

**Table 1 T1:** Difference in learning activities between blended (intervention) and non-blended (comparison) groups

**Blended learning (intervention)**	**Non-blended learning (comparison)**
**1. Prior to lesson**	
• Students view specific presentations relevant to the upcoming tutorial via YouTube	
**2. Designated EBP lesson**	
• Tutor facilitates discussion with students on key concepts to be covered in the module	• Tutor presents 30–40 PowerPoint presentation on key concepts to be covered in the module
• Students are divided into small groups (4–5 members per group)	• Tutor facilitated discussion of a previously pre-appraised article
	• Students divided into small groups (4–5 members per group) and critically appraise an article within the tutorial
	• Tutor led discussion on the critical appraisal performed by students in-class
**3. Post EBP lesson**	
• Group members to identify patient during other 'bedside teaching’	• Self-directed learning
• Whilst at the 'bedside’, students to access evidence (via mobile learning) relevant to their patient to inform decision making	
• Groups prepare oral presentation, based on their patient scenario, outlining clinical and EBP content learnt	
**4. Prior to lesson**	
• Students view specific presentations relevant to the upcoming tutorial via YouTube	
**5. Designated EBP lesson**	
• Each group presents learning experience based on their specific patient scenario during 'bedside teaching’	• Lesson repeated as per stage 2 (with new content)
• Tutor facilitates discussion based on content raised in group presentations	
• Lesson repeated as per stage 2 (with new content)	

### Intervention

Students randomised to the intervention group will receive the same theoretical concepts taught in the control group, but in a blended approach. The blended learning method integrates (i) current classroom activities (lecture/tutorial) with (ii) online and (iii) mobile learning. The online component will be provided through specific resources delivered via the Monash library website, as well as specifically designed online lectures, made available through YouTube, that students view prior to attending the respective two hour teaching block [9]. The mobile learning component will be delivered when students are on their ward rounds and interacting with patients during their existing day-to-day 'bedside teaching’ schedule. During the mobile learning, students will be required to take a detailed medical history from the patient, as they normally would during their 'bedside’ teaching, to which they will apply their EBP learning. Students will present their learning during the next two hour teaching block. The methodology for this intervention has previously been piloted in 2010–11 [10]. Whilst a two-hour block of time will be dedicated to teaching using the blended learning approach, it is anticipated that only one hour of that time will be spent in the tutorial setting, with the other hour available for students to implement their mobile and online learning activities.

### Outcome measures

Student competency in EBP will be assessed by a blinded outcome assessor using the validated Berlin tool [11]. Student self-efficacy will be assessed using Evidence-Based Practice Question (EBPQ) [12]. The EBPQ is a self-reported measure of implementation of EBP, with measures relating to self-efficacy, behaviour and attitudes toward EBP.

### Blinding

Due to the educational nature of the intervention, it is not possible to blind either the educators or the students. The outcome assessor and data analyst will be kept blinded to the allocation.

### Analyses

#### Sample size calculation

A minimum of 120 students per arm (40 from each of metropolitan Melbourne (undergraduate), rural Victoria (graduate) and Monash Malaysia (international)), will be recruited to detect a 50% difference in EBP competency (α = 0.05, β = 0.80, σ = 2.8) between groups.

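### The sample size shows no allowance for randomising tutorial groups, so the stated 0.80 cannot be taken as the power of this design

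*Protocol article*

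**What the plan says.** Under Randomisation, the unit of allocation is the tutorial group: "Participants will be randomised according to their tutorial group (i.e. cluster) by a researcher independent to the study utilising a simple cluster randomisation procedure". Under Recruitment, these are "small tutorial groups for their EBP teaching (approximately 20–25 in a group").

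Under Sample size calculation, the count is in students: "A minimum of 120 students per arm (40 from each of metropolitan Melbourne (undergraduate), rural Victoria (graduate) and Monash Malaysia (international")). They "will be recruited to detect a 50% difference in EBP competency", with the parameters "α = 0.05, β = 0.80, σ = 2.8) between groups". That section gives no intracluster correlation (ICC), design effect, cluster size or number of clusters.

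Under Analyses, the primary comparison of Berlin scores is a Student's t-test. Student type is examined by one- and two-way ANOVA. None of these is described as accounting for tutorial group.

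**The concern.** Students taught in the same tutorial group share a tutor and sessions, so their scores are likely to be correlated. When whole groups are randomised, the precision of the treatment comparison depends on the number of groups and on the ICC as well as on the number of students. The listed inputs and the planned test both suit individually randomised students, and neither suits the stated unit of randomisation.

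At stake is the meaning of the 0.80. If it came from an individual-level calculation, the difference that the trial can detect with that power is larger than planned. A reader of a null result would then credit the trial with more sensitivity than it has.

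**Working it through.** **Inputs from the protocol article.** SD σ = 2.8; α = 0.05 (two-sided assumed, as sidedness is not stated); power 0.80 (the printed label is β); n = 120 per arm; group size about 20–25.

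**Inputs assumed here.** ICC ρ = 0.01, 0.02, 0.05 and 0.10. The article gives no ICC, so these are illustrative. ρ = 0 is added to isolate the loss of degrees of freedom.

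**Step 1: the plan's own figure.** The 120 can be neither reproduced nor refuted, because the 50% has no reference mean and no value in points. The formula can only be inverted. Under individual randomisation the standard error is 2.8 × √(2/120) = 0.361. The normal approximation gives (1.960 + 0.842) × 0.361 = 1.01 points. The t distribution with 238 df gives 1.02 points, or 0.363 SD.

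**Step 2: number of clusters.** 120/20 = 6 groups per arm. 120/24 = 5 groups per arm.

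**Step 3: cluster-level calculation.** With k groups of m students per arm:

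- variance of a group mean = σ² × (ρ + (1 − ρ)/m)
- SE of the difference = √(2 × variance / k)
- degrees of freedom = 2k − 2, that is 10 for k = 6 and 8 for k = 5
- power from the non-central t distribution

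Example with m = 20, k = 6, ρ = 0.05: variance = 7.84 × (0.05 + 0.95/20) = 0.764, and SE = √(2 × 0.764/6) = 0.505. With 10 df, 80% power needs a difference of 3.11 SE, so 3.11 × 0.505 = 1.57 points. With 8 df the multiplier is 3.20.

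| Assumed ICC | Detectable with 80% power, 6 × 20 | Detectable with 80% power, 5 × 24 | Power for 1.02 points, 6 × 20 | Power for 1.02 points, 5 × 24 |
|---|---|---|---|---|
| 0 | 1.12 | 1.16 | 72% | 69% |
| 0.01 | 1.23 | 1.28 | 64% | 61% |
| 0.02 | 1.32 | 1.40 | 58% | 53% |
| 0.05 | 1.57 | 1.70 | 45% | 39% |
| 0.10 | 1.91 | 2.10 | 32% | 28% |

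The effective sample size is 120/(1 + (m − 1)ρ). At m = 20 this is 101, 87, 62 and 41 per arm for ICC 0.01, 0.02, 0.05 and 0.10.

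**Step 4: other targets.** The 1.02 points in the last two columns is solved back from n = 120 and is not a target that the protocol states. With 6 groups of 20, power for 1.4 points (half an SD) is 89%, 84%, 71% and 54% at ICC 0.01, 0.02, 0.05 and 0.10. For 2.0 points it is 95% at ICC 0.05 and 83% at ICC 0.10.

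**The case against.** A reader might infer that the trial is underpowered and that a null result could not be trusted. The documents do not support that. The target is a 50% difference of unstated size in points, and step 4 shows that a larger target could keep adequate power even with clustering.

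A reader might also take it as proved that the 120 came from an individual-level formula. It is not, because the derivation is not shown. Half an SD needs 63 per arm under individual randomisation, and 63 inflates to 120 at an ICC of about 0.038 (m = 25) to 0.048 (m = 20). An undisclosed inflation therefore cannot be strictly excluded. Nothing in the text points to one, and the unadjusted t-test points the other way.

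Four further points have weight:

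- The ICCs are assumptions. Students are "randomly placed in small tutorial groups for their EBP teaching", which limits differences between groups at the start. It does not remove correlation that arises from shared tutors and sessions.
- Forty students from each of three sites per arm fits 6 groups of 20 better than 5 of 24, so the second layout is the less likely one.
- The 120 is a minimum, so more groups may be enrolled.
- An article condenses a fuller protocol, and a missing ICC alone would be weak evidence.

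The finding does not rest on that absence. The article itself prints the inputs and names a test, and neither fits the unit of randomisation that it states.

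**Conclusion.** The point holds as a mismatch between the calculation and the design. The sample size statement shows no allowance for clustering, so the 0.80 cannot be taken as the power of a trial with about 5–6 clusters per arm.

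Relative to 1.02 points under individual randomisation, the difference detectable with 80% power rises to about 1.2–1.9 points (6 groups of 20) or 1.3–2.1 points (5 groups of 24) over assumed ICCs of 0.01 to 0.10. Even at an ICC of zero, the few degrees of freedom of a cluster-level test raise it to about 1.1–1.2 points.

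These figures rest on SD 2.8, a two-sided 5% test, equal group sizes, exactly 120 students per arm and a cluster-level analysis. They show how far the detectable difference moves. They do not show that the trial falls short of its own target, which cannot be judged until that target is given in Berlin points.

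**What to change.** Change two sections together.

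1. **Sample size calculation.** State the number of tutorial groups per arm beside the number of students, the target difference in Berlin points, and 0.80 as power. Add an assumed ICC range with its source and the resulting detectable differences. For example: with about 6 groups of 20 per arm, SD 2.8 and a cluster-level test, 80% power is reached at about 1.2, 1.3, 1.6 or 1.9 points for ICC 0.01, 0.02, 0.05 or 0.10. If 5 groups per arm is possible, give 1.3, 1.4, 1.7 and 2.1 points as well.

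2. **Analyses.** Replace the plain t-test as the primary comparison with one that accounts for tutorial group. This can be a cluster-level analysis, or a mixed model with a random effect for tutorial group and small-sample degrees of freedom. Without this change the restated power would describe a test that the plan does not use.

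The cost is a few sentences and no additional students. The downside is that the stated detectable difference becomes less favourable.
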